## Abstract

**Background:**

Polycystic ovary syndrome (PCOS) is a common endocrine condition which affects women in the reproductive age group. South Asian women with PCOS have a higher risk of insulin resistance and metabolic disorder compared to women from other ethnic backgrounds. Lifestyle interventions such as dietary advice and physical exercise are recommended as a first-line management option for infertile women with PCOS. Most of the randomized controlled trials evaluating the role of lifestyle interventions in infertile PCOS women were characterized by methodological issues. The uptake of lifestyle modifications as a treatment strategy in the South Asian population is complicated by a difficult-to-change conventional high-carbohydrate diet and limited availability of space for physical activity in the region.

**Methods:**

The study is designed as an open-label, multicentre, randomized controlled trial in South Asian women with PCOS. Women attending the fertility clinic will be screened for eligibility, and women aged between 19 and 37 years who have been diagnosed with PCOS and wishing to conceive will be invited to participate in the trial. We will include women with body mass index (BMI) between ≥ 23 and ≤ 35 kg/m^2^ and duration of infertility ≤ 3 years. We plan to randomize women with PCOS into two groups: group A will receive the intervention which will consist of individualized advice on diet and physical exercise along with a telephonic reminder system and follow-up visits, and group B (control) will receive one-time advice on diet and physical exercise. Both groups will receive up to three cycles of ovulation induction with letrozole after 3 months of randomization during the 6-month treatment period. The primary outcome of the trial will be the live birth following conception during the intervention period. The secondary outcomes include clinical pregnancy rate, ongoing pregnancy rate, miscarriage rate, ectopic pregnancy rate, stillbirth, time to pregnancy, mean weight loss, differences in anthropometric parameters, improvement in menstrual regularity and quality of life score.

**Discussion:**

The IPOS trial results could help clarify and provide more robust evidence for advocating an individualized lifestyle intervention in PCOS women who wish to conceive.

**Trial registration:**

Clinical Trial Registry of India CTRI/2023/04/051620. Registered on 13 April 2023.

**Supplementary Information:**

The online version contains supplementary material available at 10.1186/s13063-023-07466-y.

## Background

Polycystic ovary syndrome (PCOS) is a common endocrine disorder which affects women in the reproductive age group [1]. Worldwide, 1.55 million new cases of PCOS among women aged between 15 and 49 years were reported in 2017 which translated into an increase of 4.47% within a time period of 10 years [2]. The incidence of PCOS was 82.44 per 100,000 in 1 year (2017) among women in the reproductive age group [2]. There are geographical differences in the prevalence of PCOS [2]. Differences in the prevalence due to ethnicity also have been observed with a higher prevalence of PCOS observed among women from South Asian ethnicity residing in the UK compared with Caucasian women [3]. Furthermore, South Asian women with PCOS have a higher risk of insulin resistance and metabolic disorder compared to women from other ethnic backgrounds [3, 4]. These variations in PCOS prevalence due to ethnicity and geographical location have been attributed to obesity, genetic predisposition, phenotypic differences, health care access and awareness [2–4].

The underlying insulin resistance and the resultant hyperinsulinaemia are considered one of the important pathophysiological factors for PCOS [5]. Hyperinsulineamia is linked to an increase in the production of androgen and lower sex hormone-binding globulin (SHBG), resulting in excess free androgens [5]. The increased level of free androgen contributes to most of the clinical features of PCOS, such as hirsutism, acne and ovulatory dysfunction [6, 7]. More specifically, the increased levels of androgen and luteinizing hormone (LH) hypersecretion at the ovarian level leads to anovulation and oligo-ovulation, which clinically manifests as infertility in these women with PCOS [8]. Overweight and obesity worsen the underlying metabolic disturbance and clinical symptoms of PCOS [9].

Lifestyle interventions such as dietary advice and physical exercise are recommended as a first-line management option for infertile women with PCOS [6, 9]. There is a strong rationale for encouraging weight loss following lifestyle modifications as it helps improve menstrual symptoms as well as increase chances of conception in women with PCOS [10].

Several trials have been conducted in the European, North American and Australian populations evaluating the efficacy of lifestyle interventions in PCOS women [11–15]. In an open-label three-arm, randomized controlled trial (RCT) conducted at two sites in the USA (*n* = 149), the investigators compared the effectiveness of preconception lifestyle intervention before ovulation induction in PCOS women [11]. The lifestyle intervention included calorie-restricted meals, medication for weight loss and physical exercise, and the treatment period was 16 weeks. The study reported significant weight loss following lifestyle intervention and higher ovulation rates. In another single-centre RCT (*n* = 183) from The Netherlands, the authors compared lifestyle intervention in the form of diet, exercise and cognitive behavioural therapy with or without telephonic reminders versus the usual care for a period of 12 months in PCOS women who wished to conceive [12]. The authors reported significantly higher weight loss following lifestyle intervention compared to usual care. There are few trials in the South Asian population evaluating the role of diet and exercise in PCOS women [16, 17]. One of the smaller trials (*n* = 66) from India reported significant improvement in menstrual symptoms and anthropometric parameters in PCOS women following exercise and metformin [16].

Most of the randomized controlled trials evaluating the role of lifestyle interventions in infertile PCOS women were characterized by small sample size, short follow-up period and high attrition rate [10]. There were no high-quality trials with long-term follow-up evaluating the effectiveness of lifestyle interventions in PCOS women [10]. None of the published trials has included live birth rates as the outcomes, which is one of the important patient-centric fertility endpoints [10]. Furthermore, there is a definite paucity of adequately powered multicentric trials that have examined the efficacy of structured lifestyle intervention in South Asian women with PCOS.

Additionally, the uptake of lifestyle modifications as a treatment strategy in the South Asian population is complicated by a difficult-to-change conventional high-carbohydrate diet and limited availability of space for physical activity in the region [18, 19]. This limits the applicability of findings from some of the earlier trials for the PCOS population from South Asia [11, 12]. For the reasons highlighted above, we plan to conduct an adequately powered multicentric RCT to evaluate the efficacy of individualized lifestyle intervention versus usual care in Indian women with PCOS who wish to conceive.

## Method and design

### Aim of the study

The overall aim of the study is to evaluate the efficacy of individualized lifestyle intervention compared to the usual care in PCOS women who wish to conceive. We hypothesized that individualized lifestyle intervention improves fertility outcomes in PCOS women who wish to conceive when compared to the usual care. To test the hypothesis, we plan to randomize PCOS women into two groups: group A will receive the intervention which will consist of individualized advice on diet and physical exercise along with a telephonic reminder system and follow-up visits, and group B (control) will receive one-time advice on diet and physical exercise. Both groups will receive up to three cycles of ovulation induction with letrozole after 3 months of randomization during the 6-month treatment period.

### Study setting

The study is designed as an open-label, multicentre, superiority, randomized controlled trial. The study has been designed in accordance with the Standard Protocol Items Recommendations for Interventional Trials (SPIRIT) guidelines [20]. The trial has been prospectively registered with the Clinical Trial Registry of India (CTRI/2023/04/051620, registered on 13/4/2023). The sponsor and the funding agency for the trial is the Indian Council of Medical Research (ICMR), New Delhi. The sponsor will be overall responsible for the design, conduct, governance and data management of the trial as well as the final dissemination of the results.

The trial will be conducted at five sites across India which are as follows: (1) Division of Reproductive Medicine, Department of Obstetrics and Gynaecology, All India Institute of Medical Sciences (AIIMS), New Delhi; (2) Department of Reproductive Medicine and Surgery, Christian Medical College (CMC), Vellore, Tamil Nadu; (3) Department of Obstetrics and Gynaecology, Post-graduate Institute of Medical Education and Research (PGIMER), Chandigarh; (4) Department of Obstetrics and Gynaecology, All India Institute of Medical Sciences (AIIMS), Bhubaneswar, Odisha; and (5) Department of Obstetrics and Gynaecology, Sawai Man Singh (SMS) Medical College, Jaipur, Rajasthan. All the sites are medical colleges representing populations from northern, southern, eastern and western regions of India and will have investigators from the endocrine speciality to provide inputs to the design of lifestyle interventions and facilitate the metabolic assessments.

### Inclusion and exclusion

Women attending the fertility clinic will be screened for eligibility. The inclusion criteria will be (i) women aged between 19 and 37 years who have been diagnosed as PCOS by the Rotterdam criteria and wishing to conceive, (ii) body mass index (BMI) ≥ 23 kg/m^2^ but ≤ 35 kg/m^2^ and (iii) duration of infertility ≤ 3 years. The exclusion criteria will be as follows: (i) women planning to take medical treatment at hometown and not available for follow-up period (6 months); (ii) does not have a mobile phone in the house; (iii) pregnancy; (iv) late-onset congenital adrenal hyperplasia (CAH) and androgen secreting tumours; (v) diabetes mellitus, uncontrolled hypothyroidism (TSH > 10 IU/ml), hyperprolactinemia (> 70 ng/ml), bronchial asthma, chronic kidney and liver disease; (vi) prediabetic on metformin or insulin sensitizers or other anti-diabetic medicines; (vii) inflammatory arthritis or any lower limb pathology which precludes exercise; (viii) gastro-intestinal conditions (e.g. ulcerative colitis, Crohn’s disease, coeliac disease) which require special dietary advise; (ix) on anti-psychiatric medications; (x) undiagnosed uterine bleeding; (xi) medical conditions which are contraindications for pregnancy; (xii) previous history of receiving > 6 ovulation induction cycles with letrozole or laparoscopic ovarian drilling; (xiii) previous history of bariatric surgery or planning other strategies for weight loss beyond the trial intervention including but not limited to Fad diets, intra gastric procedures or on weight loss medication; and (xiv) other known causes of infertility which are indications for assisted reproductive technology (ART) treatment, namely severe endometriosis, severe male factor infertility, male partner with azoospermia and documented severe tubal pathology.

Newly detected prediabetics will be included only if they are willing for an initial trial of lifestyle intervention for glycaemic control. We will repeat glycosylated haemoglobin (HbA1c) at 3 months interval, post-randomization, to assess the glycaemic control. If the Hb1Ac is ≥ 6.5%, then initiation of metformin will be considered, and the participant will be followed up as per protocol but will not be considered for per protocol analysis.

The presence of diabetes and prediabetes will be defined based on the criteria from the American Diabetes Association [21]. Individuals with fasting plasma glucose value ≥ 126 mg/dl and/or 2-h plasma glucose value of ≥ 200 mg/dl and/or HbA1c ≥ 6.5% will be diagnosed to have diabetes. Those with a fasting plasma glucose value between 100 and 125 mg/dl with a 2-h plasma glucose < 140 mg/dl (impaired fasting glucose) and/or a 2-h plasma glucose between 140 and 200 mg/dl with a fasting plasma glucose less than 100 mg/dl (impaired glucose tolerance) OR HbA1c (5.7–6.4%) will be diagnosed as pre-diabetics. Those with fasting plasma glucose < 100 mg/dl and a 2-h plasma glucose < 140 mg/dl and HbA1c < 5.7% will be considered to have normal glucose.

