### Medical treatment 3 months post-randomization for intervention and control arm

These will be as per standard infertility guidelines starting with letrozole. Ovarian induction may be followed with timed intercourse or IUI (combined male factors such as sexual dysfunction) as per the participant’s profile. The treatment will be given for up to 3 cycles depending on the unit policy, while the lifestyle intervention follow-up will continue in the interventional arm over the next 3 months, to be completed for 6 months.

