### Sample size calculation

No previous data is available on live birth following individualized lifestyle intervention in PCOS women who wish to conceive. From previous study performed in one of the trial sites, the live birth rate following usual care which consisted of one-time lifestyle advise and ovulation induction with Letrozole for up to five treatment cycles, was reported as 30% [25]. Due to uncertainty about the likely event rate (live birth rate) in the intervention arm, it was assumed that to convince the clinicians and patients to adopt a change in practice, a modest improvement of 10% in live birth would be required.

For alpha error set at 0.05 and power being 90%, to detect a clinically relevant difference of 10% in the live birth rate following individualized lifestyle intervention, the calculated sample size will be 473 in each arm (total sample size 946). Assuming an attrition of 20%, the total sample size was 1183. We rounded off the total sample size to 1200 with 600 in each arm. With 5 centres participating in the study each site shall recruit 240 subjects each.

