We plan to adjust the results for the following covariates: (i) number of letrozole cycles. Logistic regression analysis will be used to adjust the covariates effectively the adjusted effect size will be presented as an odds ratio (95% CI) for binary outcomes. All the analyses will be performed using STATA/IC 16.0.

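### The 30% control live-birth rate comes from up to five letrozole cycles, but the trial gives up to three; the sample-size section neither adjusts for this nor shows how power and the implied effect depend on it

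*Protocol article*

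**What the plan says.** Protocol article, Sample size calculation: the planning rate is introduced with "From previous study performed in one of the trial sites, the live birth rate following usual care", and that usual care was one-time lifestyle advice plus "ovulation induction with Letrozole for up to five treatment cycles, was reported as 30" per cent. The target is absolute and is justified as what would change practice: "a modest improvement of 10% in live birth would be required". The calculation then runs "For alpha error set at 0.05 and power being 90" per cent, and "the calculated sample size will be 473 in each arm (total sample size 946". With 20% attrition this becomes 1183, rounded to 1200.

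Protocol article, Medical treatment 3 months post-randomization: "The treatment will be given for up to 3 cycles depending on the unit policy". The Aim of the study section gives the same ceiling for both arms and starts letrozole 3 months after randomisation, within a 6-month treatment period. The Primary outcome section counts live births only from conceptions within 6 months of randomisation.

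Protocol article, Inclusion and exclusion, criterion (xii), excludes women with "previous history of receiving > 6 ovulation induction cycles with letrozole or laparoscopic ovarian drilling". Women with none to six earlier letrozole cycles are therefore eligible.

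Protocol article, statistical analysis section: "We plan to adjust the results for the following covariates: (i) number of letrozole cycles". No other covariate is named. Randomisation is stratified by site and BMI.

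**The concern.** The control rate is the one empirical input to the sample size, and it was observed under a longer letrozole course than this trial offers. The sample-size section makes no adjustment for the shorter course and gives no sensitivity range.

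Two things depend on it. The first is how ambitious the target is: ten points on 30% is a one-third relative gain, and on a lower base it is a larger one, so describing it as modest relies on the 30%. The second is power if lifestyle advice multiplies the chance of live birth instead of adding a fixed number of points. The Discussion lists adequate power as a main strength, and a reader cannot tell how far that rests on a five-cycle figure.

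Earlier letrozole exposure is a related gap. Eligible women may already have had a course as long as the one behind the 30%, yet the article does not say whether the source study admitted such women. The only letrozole covariate in the plan is an unqualified cycle count. It most naturally means cycles given during the trial. That is a post-randomisation quantity, which may itself depend on how soon a woman conceives, and it cannot stand in for exposure before entry.

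**Working it through.** **Inputs from the protocol article.** Control 30%, intervention 40%, alpha 0.05 (two-sided reproduces the figure), power 90%, 1:1 allocation, 473 per arm, 20% attrition, up to five cycles in the source, up to three in the trial.

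**1. Reproduce the stated size.** Unpooled normal approximation: n = (1.960 + 1.282)² × (0.30×0.70 + 0.40×0.60) / 0.10² = 472.8, so 473 per arm. The pooled-variance formula gives 477. Attrition: 946 / 0.80 = 1182.5, so 1183. The arithmetic is sound.

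**2. Translate five cycles to three (assumption: constant chance per cycle, all five cycles taken by women without success).** Per cycle: 1 − 0.70^(1/5) = 0.0689. Over three cycles: 1 − 0.70^(3/5) = 0.193.

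This is illustrative. Five is a ceiling and the average number delivered is not given. If the effective number were four, the same formula gives 1 − 0.70^(3/4) = 0.235; if it were three, 0.30. Conceptions in months 0–3, before letrozole starts, would also raise the rate.

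**3. Power at 473 per arm.** With d the difference and p̄ the mean of the two rates, power = Φ{[d√n − 1.960√(2p̄(1−p̄))] / √(p₁(1−p₁) + p₂(1−p₂))}.

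- 30% v 40%: (2.175 − 1.322) / 0.671 = 1.271, power 89.8%.
- 19.3% v 29.3%: (2.175 − 1.188) / 0.602 = 1.639, power 94.9%.
- 19.3% v 25.7%: (1.397 − 1.157) / 0.589 = 0.407, power 65.8%.

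| Assumed control rate | Risk ratio implied by +10 points | Power, +10 points | Intervention rate at risk ratio 4/3 | Power, risk ratio 4/3 |
|---|---|---|---|---|
| 19.3% | 1.52 | 94.9% | 25.7% | 65.8% |
| 20% | 1.50 | 94.5% | 26.7% | 67.9% |
| 25% | 1.40 | 92.0% | 33.3% | 80.6% |
| 28% | 1.36 | 90.6% | 37.3% | 86.6% |
| 30% | 1.33 | 89.8% | 40.0% | 89.8% |

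**4. Size needed for 90% power at 19.3% (pooled formula).** Absolute 10 points: 385 per arm. Risk ratio 4/3: 884 per arm. An intermediate assumption, the planned odds ratio of (0.40/0.60)/(0.30/0.70) = 1.56, gives 19.3% v 27.1% and 81% power at 473 per arm.

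**The case against.** The strongest reply is that the plan's target is an absolute 10 points, set as the gain that would change practice. On those terms a lower control rate raises power, and 473 per arm is conservative. This stands. A reader might infer that the trial is underpowered or that its 90% is lost; the documents do not support that. The loss appears only under a proportional effect, which the plan does not assume. What remains is that ten points is a threshold of interest and not an estimate of effect, and on a lower base it requires a larger relative effect.

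The 19% is also fragile, for the reasons given with the calculation, and if women differ in their chance of success, successes fall disproportionately in the early cycles. All of this moves the three-cycle rate towards 30%. That argues for stating a range, not for keeping the single five-cycle figure without comment.

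It could be said that 600 per arm will be randomised. With no dropouts, power at 19.3% and risk ratio 4/3 would be 76%. But dropouts without outcome information are counted as no live birth. With 20% such dropouts in each arm the comparison is 15.4% v 20.6%, with power about 64%. The extra women do not remove the sensitivity.

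Three further inferences should not be drawn from the prior-cycle criterion. That the 30% is wrong for the eligible population is unproven: the source study's entry criteria are not given, and it may also have admitted previously treated women. Mixing women with different chances does not add variance to the primary comparison, because a binary outcome has variance p(1−p) at the marginal rate, which the formula already uses. And nothing in the documents shows that women with earlier cycles are resistant to letrozole or that the count strongly predicts live birth.

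Finally, randomisation protects the comparison without this covariate, and further covariates could be left to an analysis plan. That is fair, but the protocol does name a letrozole covariate, and names it in a way that most naturally means the post-randomisation count.

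**Conclusion.** The point holds in a limited form. The 30% does not describe the treatment course in this trial (up to three cycles, conception within 6 months), and it is not shown to describe women with up to six earlier cycles. The stated sample size is computed correctly, and for the plan's own absolute target it is sufficient across 19–30%, with power from about 95% down to 90% at 473 per arm.

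The consequence is in interpretation. At about 19% the target means a risk ratio of 1.52 instead of 1.33. If the effect is proportional at 1.33, power is about 66% at 19%, 81% at 25% and 87% at 28%. The 19% rests on a constant chance per cycle over five full cycles and no allowance for months 0–3. The true rate may be nearer 30%, in which case little changes.

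**What to change.** In Sample size calculation, keep the source figure but say that it comes from up to five cycles. State the control rate as an assumed range for up to three cycles in the eligible women (for example 19–30%), and give power and implied relative effect across it for an absolute 10-point gain and for a constant risk ratio; the table above would serve.

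In the statistical analysis section, prespecify the number of letrozole cycles received before randomisation as a baseline covariate for the primary outcome, and say explicitly whether the covariate now listed means cycles before or after randomisation.

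No change to sample size, eligibility or treatment is proposed. The cost is a paragraph of text and one baseline item that screening for criterion (xii) already obtains. The downside is a power statement that looks less favourable if the effect is proportional.

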### Dropout criteria

Those participants who are randomized but do not report for further follow-up visits at 3 and 6 months will be considered as dropouts. Randomized participants who withdraw their consent also will be considered as dropouts. The participants who report for the follow-up visit but do not comply with dietary and/or exercise advice will be considered as either non-compliant or partially compliant but will not be considered as “dropouts” as per the agreed criteria shown in Table 1.

**Table 1 Tab1:** Compliance and dropout criteria for inclusion in per-protocol/ITT or additional analysis

